## Methods/design

### Trial objectives

The primary aim of this study is to collect preliminary Phase I/IIa proof-of-concept trial data from people with early AMD in one eye and advanced nAMD in the fellow eye, recruited from a hospital nAMD clinic, in order to assess the impact of low-level night-time light therapy, compared with no intervention, on disease progression in the eye with early AMD. A further main aim of this trial is to assess safety of the mask in the cohort of participants with AMD.

The secondary aims of the study are to:

1. Establish the effect of low-level night-time light therapy, compared with no-treatment control, on secondary outcome measures, including: change in drusen volume from baseline in the eye with early AMD; ranibizumab retreatment rates in the fellow eye with nAMD; progression of early AMD on the basis of change in functional outcome measures; change in health-related quality of life (assessed using the EuroQol EQ-5D instrument); change in self-reported visual function assessed using the 48-item Veterans Affairs Low-Vision Visual Functioning Questionnaire (VA LV VFQ-48).

2. Establish the acceptability of low-level night-time light therapy in people with AMD by monthly qualitative interviews.

3. Determine the effect of low-level night-time light therapy on sleep patterns by conducting the Pittsburgh Sleep Quality Index (PSQI) questionnaire every month with both intervention arms by interview with the study investigator.

4. Establish the relationship between baseline functional biomarker outcomes and the severity of AMD (assessed using the simplified Age-Related Eye Disease Scale (AREDS) and initial drusen volume).

5. Evaluate the ability of all clinical tests to act as prognostic biomarkers for AMD progression.

6. Evaluate the ability of all clinical tests to act as predictive biomarkers for low-level night-time light therapy in people with AMD.

7. Compare the sensitivity of all clinical tests to disease progression over 12 months.

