### Recruitment

Sixty participants will be recruited to the trial. Ophthalmologists will identify potential trial participants who are attending for their first appointment at the nAMD clinic at Bristol Eye Hospital, and will provide them with an information sheet and ask for their permission to be contacted by the study investigators. The potential participants will be contacted at least 2 days after their receipt of the information sheet, and invited to meet the study investigator at their next visit to the nAMD clinic (approximately 1 month later) to discuss the trial, provide consent if they choose to participate, and carry out some basic screening tests. Participants will be informed after this screening visit whether they are eligible to take part in the study. Owing to the low number of patients required to participate in the study it is planned for the trial and data collection to take place principally at a single NHS centre, that is, the Bristol Eye Hospital. If needed, additional participants will be recruited from supplementary recruitment centres to ensure that targets are met.

Forty control participants and participants with grade 1 AMD (AREDS simplified scale [45]) for the baseline cross-sectional analysis will be recruited by local optometrists in Bristol and Cardiff, from a database of elderly volunteers, from the Bristol Eye Hospital, from the list of research volunteers at the Cardiff University Eye Clinic and from staff and students of Cardiff University.

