### Randomization

Participants will be stratified according to risk of AMD progression (using the AREDS simplified scale [45]), and randomly allocated to receive either the light mask or no intervention in a 1:1 ratio using computer-generated random permuted blocks (both groups will continue to receive ranibizumab injections as required for the fellow eye). The study investigator will be provided with three piles of envelopes by the chief investigator, in order to randomize the participant to either the intervention or control arm of the study. Each pile relates to a different stratum of randomization, that is, grade 2, 3 or 4 of AMD, according to the AREDS simplified scale. The envelopes in each pile will be numbered, and will contain the randomization allocation for each participant.

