### Statistical methods

It should be noted that, as a Phase I/IIa proof-of-concept study, this research is designed to assess the acceptability of this therapy for the participants, and to provide preliminary data to support a larger Phase III randomized controlled trial in the future, and so is not powered to detect small effect sizes. To maximize retention, all follow-up visits will be timed to coincide with scheduled appointments at the nAMD clinic. We will aim to recruit 60 people, which, allowing for 15% dropout through the year, should leave a final cohort of 51. This will be sufficient to detect a 50% reduction in people showing progression at a probability level of 0.2, with a power of 80%, and a change in the time constant of cone adaptation of 1 minute to be detected at a probability level of 0.05, with a power of 80%. The additional 40 participants enrolled into the cross-sectional part of the study will allow a total cohort of *n* = 100 to address secondary aim 4.

Analysis will be carried out on an intention-to-treat basis. There will be no interim analysis, but conversions to nAMD in the eye with early AMD at baseline, and ranibizumab retreatments for the fellow eye, will be recorded at each participant visit to the nAMD clinic for safety monitoring purposes.

This trial will primarily be concerned with providing information about the safety of the device in the treatment of AMD, and the magnitude of any treatment effect. On this basis, descriptive statistics will be carried out to summarize the demographic characteristics of the two groups, as well as the proportion of individuals showing disease progression in each group, the magnitude of changes in secondary outcome measures, including drusen volume, measures of visual function, and the self-report tests, and the fellow eye retreatment rates.

The primary outcome measure will be the proportion of patients demonstrating disease progression at 12 months. Comparisons will be performed using stratified Mantel-Haenszel tests and presented as forest plots.

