Formal statistical analysis will also include linear regression analysis to investigate changes in drusen volume controlling for intervention arm, baseline drusen volume and patient characteristics (such as age, vitamin supplement intake and history of smoking). Analysis of covariance (ANCOVA) will be carried out to compare the change in secondary outcome measures (for example, drusen volume, functional tests, self-report measures) and the ranibizumab retreatment rates over 12 months between the two intervention arms, controlling for the characteristics listed previously. Note that all analysis except for the ranibizumab retreatment rate pertains to the eye with early AMD. This will address secondary aim 1. To meet our fourth secondary aim, which is to establish the relationship between baseline functional biomarker outcomes and the severity of AMD, we will carry out a one-way analysis of variance (ANOVA) to compare the mean results at baseline between participants with grades of AMD in each group on the AREDS simplified scale. This analysis will take place when the baseline data collection is complete. To assess the ability of the clinical tests to act as prognostic and predictive biomarkers, receiver operating characteristics curves will be constructed to plot the sensitivity and specificity of the baseline measures in predicting outcomes within the control and intervention arms, respectively. This will address secondary aims 5 and 6. When the trial is completed, linear regression analysis will be used to determine how well the change in the functional measures relate to the change in our primary outcome measure (drusen volume), which is a validated biomarker for disease progression. This will address the seventh secondary aim.

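### Secondary aim 4 names only an omnibus ANOVA across ordered AREDS grades; adding a linear trend contrast would give the direction and size of the relation and, if that relation is near-linear, more power

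*Protocol article*

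**What the plan says.** Aim 4, under Trial objectives, is to "Establish the relationship between baseline functional biomarker outcomes and the severity of AMD", with severity "assessed using the simplified Age-Related Eye Disease Scale (AREDS) and initial drusen volume". The Statistical methods section names one analysis for it: "one-way analysis of variance (ANOVA) to compare the mean results at baseline between participants with grades of AMD in each group on the AREDS simplified" grading scale. No trend contrast or regression on grade is mentioned.

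The same section says that the 40 additional participants "will allow a total cohort of *n* = 100 to address secondary aim 4". The grades come from two sources:

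- The trial participants supply three levels. Under Randomization: "Each pile relates to a different stratum of randomization, that is, grade 2, 3 or 4 of AMD, according to the AREDS simplified scale".
- The cross-sectional participants supply two more. Under Recruitment: "Forty control participants and participants with grade 1 AMD".

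Pooled, that makes five ordered levels: controls and grades 1, 2, 3 and 4. The document gives no significance level, effect size, power or number per grade for aim 4.

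**The concern.** The protocol itself treats the scale as ordered: aim 4 uses it to measure severity, and the randomization is stratified on it as a measure of progression risk. The omnibus F test does not use that order. With five grades it spends four degrees of freedom on differences of any pattern, and swapping the grade labels leaves F and the p-value unchanged. A significant result shows that some means differ. It does not show that function worsens as severity rises, or by how much per grade.

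Two things are at stake. One is interpretation: the direction and size of the relation would have to be read informally from the grade means. The other is efficiency: if the relation is close to linear, an F test spread over four degrees of freedom can miss a decline that a directed test would find. The randomised comparison and the safety assessment are not affected.

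**Working it through.** **The plan's own figure.** The only number given for aim 4 is its cohort size: 60 trial + 40 cross-sectional = 100. It reproduces.

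**Inputs.**
- From the protocol article: N = 100; five levels if pooled (controls and grade 1 from Recruitment, grades 2 to 4 from Randomization).
- Assumed, because the document does not state them: two-sided 5% level, normal errors with common variance, a range of effect sizes and, where the pattern is not linear, 20 participants per grade.

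**Method.** Let λ be the noncentrality, that is, the between-grade sum of squares of the true means divided by the error variance.
- Omnibus power = P(F′(4, 95; λ) > 2.467).
- Trend power = P(F′(1, 98; λr²) > 3.938), where r² is the squared correlation between equally spaced grade scores and the true means. For an exactly linear pattern r² = 1.

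**Linear pattern, five grades, N = 100.**

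| λ | Trend power | Omnibus power | Gap (points) |
|---|---|---|---|
| 3.92 | 50% | 29.9% | 20.1 |
| 5.00 | 60% | 37.8% | 22.2 |
| 6.30 | 70% | 46.9% | 23.1 |
| 8.01 | 80% | 58.1% | 21.9 |
| 10.72 | 90% | 72.6% | 17.4 |
| 13.25 | 95% | 82.4% | 12.6 |
| 18.74 | 99% | 94.1% | 4.9 |

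The largest gap is 23.1 points. For a linear pattern this comparison does not depend on how the 100 are spread over the grades.

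**Fewer grades.** If only the 60 trial participants are used (grades 2 to 4), the omnibus test has 2 and 57 degrees of freedom. Trend powers of 60%, 70%, 80% and 90% then go with omnibus powers of 48.7%, 58.8%, 70.0% and 82.8%, so the gap is about 7 to 11 points. With two levels, as in the cross-sectional participants alone, the tests are the same and the gap is 0.

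**Other patterns.** Here λ = 12.54, at which the five-grade omnibus test has 80% power, with 20 per grade.

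| True pattern | r² | Trend power (omnibus 80%) |
|---|---|---|
| Linear | 1.00 | 93.9% |
| Rise to grade 2, then plateau | 0.78 | 87.3% |
| One step, between grades 1 and 2 or 2 and 3 | 0.75 | 85.9% |
| Only grade 4 differs | 0.50 | 69.8% |
| Only controls differ | 0.50 | 69.8% |
| Only grade 1 or only grade 3 differs | 0.125 | 23.6% |
| Only grade 2 differs | 0 | 5% |

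The trend test gains on near-linear patterns and on mid-scale steps. It loses about 10 points when the change is confined to either end of the scale, and most of its power when the pattern is non-monotone.

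**The case against.** The strongest reply is that the plan contains no error here. Comparing means across severity grades is a standard answer to a question about a relationship, and it also detects threshold patterns that a trend test can miss. That stands, and it is why the ANOVA should be kept.

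A second reply is that contrasts usually belong in the analysis plan, which is not shown. This stands in part. If that plan already specifies a trend contrast, the point is met. But the article fixes the method for aim 4 by name, and the comment is on that stated choice, not on missing detail.

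A third reply is that a single slope imposes structure. It assumes equal spacing between grades. Moreover, controls and grade 1 come from the cross-sectional recruitment, whereas the grade 2 to 4 participants are trial participants with neovascular AMD in the fellow eye. The step from grade 1 to grade 2 is therefore also a change of recruitment source and fellow-eye status, and a pooled slope would absorb that difference. This stands and shapes the fix.

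The wording that the grades are compared in each group is also ambiguous. The stated cohort of 100 for this aim favours the pooled reading, but an analysis within each cohort would leave a smaller gap or none.

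Two stronger readings are tempting. One is that the plan simply loses about 20 points of power. The document gives no effect size, level or shape from which that could follow; it holds only for a linear relation over five pooled grades with mid-range power. The other is that aim 4 asks for a graded relation which the ANOVA fails to test. The aim speaks only of a relationship and names no shape.

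**Conclusion.** The point holds as one of efficiency and interpretability on an exploratory secondary aim. The named test is valid, but it ignores the order of the grades and gives no direction or per-grade size.

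The power gain from a trend contrast is conditional. It is 17 to 23 points when the relation is near-linear over five pooled grades, N = 100, the level is 5% and trend power lies between 60% and 90%. It is smaller for large effects (about 5 points at 99% trend power), about 10 points for grades 2 to 4 alone, and negative if only one end of the scale differs or the pattern is non-monotone. Which case applies cannot be settled from the document, so the figures support adding a contrast, not dropping the ANOVA. It is a cheap improvement.

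**What to change.** In the Statistical methods section, next to the ANOVA for aim 4:

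1. Add a pre-specified linear trend contrast across ordered AREDS grade, and report the change in each functional measure per grade with its 95% interval.
2. Keep the omnibus test, or the remaining three degrees of freedom as a test of departure from trend, and show the grade means.
3. Report the trend within the trial cohort (grades 2 to 4) as well as pooled, so that the cohort difference between grades 1 and 2 can be seen.
4. State whether the ANOVA is pooled over all 100 participants or run within each cohort.

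The cost is a few sentences; no new data are needed, and the contrast comes from the same fitted model. The downsides are that the contrast has less power for an effect confined to one grade and that the slope assumes equally spaced grades. The retained tests and the grade means keep such patterns visible.

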### Outcome measures

This study includes two co-primary outcome measures, reflecting structural status and functional status.

1. The proportion of people who show ‘disease progression’ in the eye with early AMD during the 12 months of the study based on an increase in drusen volume beyond test-retest repeatability limits or a progression to advanced AMD. Software available for the Cirrus optical coherence tomography (OCT) system allows automated assessment of drusen volume. Irrespective of initial drusen volume, approximately 50% of people with AMD show a significant increase in drusen volume over the 12-month study period, that is, beyond test-retest 95% confidence intervals [42]. Conversion to advanced disease will also be considered to be an indicator of disease progression in this analysis. Data from a trial on a similar group indicates that about 10% of people meeting our inclusion criteria will develop advanced AMD within 12 months [43]. Hence, 60% of participants might be expected to show progression based on increased drusen volume or progression to late AMD. The development of advanced AMD will be determined on the basis of ophthalmologist diagnosis at the monthly follow-up appointments at the nAMD clinic.

2. The rate of retinal adaptation (time taken for photoreceptors to recover their sensitivity after being exposed to a bright adapting light).

Secondary outcome measures include: the change in drusen volume over the 12 month follow-up period; the number of ranibizumab retreatments required during the year in the fellow eye with nAMD (assessed through review of medical records at the end of 12 months); changes in visual function including chromatic thresholds, visual acuity and psychophysical 14 Hz flicker thresholds; self-report outcome measures, including health-related quality of life (EQ-5D) and visual function (VFQ-48) [44]; a sleep quality questionnaire (PSQI) and a semistructured interview (conducted monthly by interview) to determine intervention acceptability.

To obtain detailed information about the time course of any therapeutic action, the primary and the first of the secondary outcome measures (based on drusen volume) will be assessed at baseline and then at monthly intervals (using OCT images obtained at the regular nAMD clinic follow-up appointments).

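### Secondary aim 6 (markers predictive of the light therapy) is to be answered from ROC curves within the intervention arm, which cannot separate a marker of treatment response from a purely prognostic one

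*Protocol article*

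**What the plan says.** The Trial objectives section of the protocol article keeps two biomarker aims apart. Aim 5 is to "Evaluate the ability of all clinical tests to act as prognostic biomarkers for AMD progression". Aim 6 is to "Evaluate the ability of all clinical tests to act as predictive biomarkers for low-level night-time light therapy in people with AMD".

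The Statistical methods section gives one analysis for both: "To assess the ability of the clinical tests to act as prognostic and predictive biomarkers, receiver operating characteristics curves will be constructed", in order to "plot the sensitivity and specificity of the baseline measures in predicting outcomes within the control and intervention arms, respectively". It then states: "This will address secondary aims 5 and 6". Read with the order of the two marker types, the closing *respectively* pairs prognostic with the control arm and predictive with the intervention arm.

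The same section describes a linear regression and an ANCOVA that control for or compare the arms. These serve secondary aim 1 and name no interaction between a baseline test and arm. No other analysis is tied to aim 6.

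**The concern.** A baseline test is predictive of a therapy when the effect of the therapy differs by the level of the test. That is a contrast between arms. Discrimination within the treated arm answers another question: among people who wore the mask, does the test separate those who progressed from those who did not? Any test that is prognostic whatever the treatment will do so.

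The error can run both ways. A purely prognostic test can look predictive. A test that truly modifies the effect, but is related to outcome only in untreated eyes, shows nothing in the treated arm and is missed.

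The study is meant to supply preliminary data for a Phase III trial. A test wrongly carried forward as a marker of response could influence who is enrolled there.

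**Working it through.** **Inputs from the protocol article**
- Control progression, Outcome measures: "Hence, 60% of participants might be expected to show progression based on increased drusen volume or progression to late AMD".
- Effect, Statistical methods: "sufficient to detect a 50% reduction in people showing progression at a probability level of 0.2, with a power of 80" per cent. A 50% reduction takes 60% to 30%.
- Size, Statistical methods: "allowing for 15% dropout through the year, should leave a final cohort of 51". 60 × 0.85 = 51, or 25.5 per arm at 1:1.

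**The plan's own figure.** No figure is given for aim 6. The power of the progression comparison can be checked, to confirm that 60% versus 30% is the intended scenario. With two-sided α = 0.2 (z = 1.2816; sidedness is not stated) and mean proportion 0.45:

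power = Φ[(0.30·√25.5 − 1.2816·√(2·0.45·0.55)) / √(0.6·0.4 + 0.3·0.7)] = Φ[(1.515 − 0.902) / 0.671] = Φ(0.914) = 0.82.

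This agrees with the stated 80%. The point about aim 6 does not depend on it.

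**Model for the check.** logit P(progression) = a(arm) + b·x, with x a standard-normal baseline marker and the same b in both arms, so there is no interaction on the odds-ratio scale. The intercepts are set to give 60% and 30% overall. The documents give no marker strength, so b = 0.5, 1.0 and 1.5 per SD are assumed. The plan names no test of an ROC curve, so a Mann-Whitney test at 5% two-sided is assumed. The interaction is tested by likelihood ratio at 5%. Each scenario had 2,000 runs at 25 per arm and 1,000 at 150 per arm. Ranges in the table come from repeat runs.

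| b per SD (both arms) | AUC control | AUC treated | Treated-arm ROC significant, 25 per arm | Same, 150 per arm | Interaction test significant, 25 per arm |
|---|---|---|---|---|---|
| 0.5 | 0.63 | 0.63 | 15–17% | 73% | 6% |
| 1.0 | 0.74 | 0.74 | 45–47% | 99.9% | 7% |
| 1.5 | 0.81 | 0.82 | 71–73% | 100% | 8% |

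With an assumed cut-off of AUC ≥ 0.70 in place of a test, the treated-arm curve qualifies in 29%, 66% and 88% of trials at 25 per arm. Larger samples do not cure the problem: the treated-arm curve becomes more often significant, while the interaction test stays near 5% (4% to 7% at 150 per arm).

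**The reverse error.** Let the marker act in controls only (b = 1 in controls, 0 under treatment; 1,000 runs). The treated-arm AUC is 0.50 and the curve is significant in about 5% of trials at either size, although the marker modifies the effect. If it acts under treatment only, the treated-arm AUC is 0.74, the same as for the purely prognostic marker with b = 1. The treated arm alone cannot tell these two apart.

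**What the interaction test can do at this size.** Its power for a marker acting in one arm only (b = 1) is about 35% at 25 per arm, against 96% to 97% at 150 per arm.

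**Scale.** For b = 1 in both arms the intercepts are 0.490 (control) and −1.018 (treated), which give:

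| Marker level | Control | Treated | Risk difference | Risk ratio |
|---|---|---|---|---|
| −2 SD | 18% | 5% | 13 points | 0.26 |
| Mean | 62% | 27% | 35 points | 0.43 |
| +2 SD | 92% | 73% | 20 points | 0.79 |

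A marker with no interaction on the odds-ratio scale can therefore still alter the effect on the risk scales.

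**The case against.** **It is one of seven secondary aims in a proof-of-concept trial.** This stands, and it limits the severity. The trial is described as primarily about safety and the magnitude of any effect. No primary analysis, safety rule or design feature depends on the biomarker curves.

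**The curves are descriptive and carry no decision rule.** This also stands. A reader might infer that every good prognostic test will be declared predictive, or that this is certain. The document does not support that: it gives no AUC threshold and no test, and the rates above depend on assumed marker strengths and an assumed test.

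**A marker with equal odds ratios in both arms is not necessarily useless for choosing whom to treat.** Correct. It would be tempting to say that its predictive value is nil, but that holds only on the odds-ratio scale, as the last table shows. The protocol itself states its target effect as a percentage reduction in people progressing. The example shows that a one-arm AUC is uninformative about effect modification, and no more.

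**Using controls alone for aim 5 wastes half the data.** A reader might add this as a second fault. It is not one: prognosis without the mask is a legitimate target, and the control arm estimates it directly.

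**Curves are drawn in both arms, so they can be compared.** An informal comparison is possible. However, the plan states none and ties each curve to a different aim.

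**The detail may be in a fuller document.** The article does not leave the method open. It names one, assigns the arms and says that it addresses both aims. That is a stated mismatch and not an omission.

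**Conclusion.** The method stated for aim 6 is wrong as written: ROC curves within the intervention arm do not estimate whether the effect of the mask differs by baseline test. This follows from the definition of a predictive marker and needs no assumption. The size is illustrative. With equal log-odds of 0.5 to 1.5 per SD in both arms and progression of 60% versus 30%, a marker without interaction on the odds-ratio scale gives a significant treated-arm curve in about 15% to 73% of trials with 25 per arm. A marker that acts only in controls is picked up no more often than chance.

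Severity is moderate and confined to secondary aim 6. It is a risk of mislabelling, not a certain result, and it touches neither the co-primary comparisons nor aim 5.

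**What to change.** For aim 6, replace the treated-arm ROC analysis with a model for progression on all randomised participants containing arm, the baseline marker and their interaction. Report the interaction with its confidence interval. Also show the treatment effect on the absolute-risk scale across marker levels, since the odds-ratio scale alone can mislead.

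Label the analysis exploratory and state how many tests are examined. Keep the model small or penalised. Expected events are 25.5 × 0.6 + 25.5 × 0.3 ≈ 23, so three coefficients leave about 23/3 ≈ 7.7 events each. Adding the three-level AREDS stratum (two more coefficients) leaves 23/5 = 4.6.

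Keep the control-arm ROC curves for aim 5, and the treated-arm curves as description only.

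The cost is analysis wording, with no new data, visits or participants. The downside is an imprecise interaction with about 51 participants (power of about 35% in the example above), and the report should say so.
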